#### Diagnostic criteria

2.4.1

According to the Bologna Conference standards of the European Association for Human-Assisted Reproduction, *the Guidelines Outlined in the Expert Consensus on the Clinical Diagnosis and Management of Diminished Ovarian Reserve 2022*, the diagnostic criteria for DOR include the following:Anti-Müllerian hormone (AMH) < 1.1 ng/mL;Antral follicle count (AFC) < 5–7 follicles in both ovaries during the early follicular phase (days 2–4 of the menstrual cycle)Basal follicle-stimulating hormone (FSH) ≥ 10 IU/L in two consecutive menstrual cycles.

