#### Primary outcome

2.7.1

AFC: At baseline (week 0), after the 16-week intervention (week 16) and at the end of the follow-up period (week 32), transvaginal ultrasound examinations will be performed to assess the number of 2–9 mm antral follicles in both ovaries. The total AFC will be calculated as an important indicator of ovarian reserve function.

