### Sample size estimation

2.8

The sample size was calculated based on the primary outcome, namely the change in AFC from baseline to week 16. Data from our previous study indicated that the mean AFC level after YYRM treatment in the intervention group was 4.16 ± 0.86, while the change in the waitlist group was 3.00 ± 1.69. Assuming a minimal clinically important difference of 1.8 between the two groups, with a one-sided significance level of *α* = 0.025 and statistical power of 90% (*β* = 0.10), the required sample size was estimated to be 56 participants (28 per group). Considering a potential dropout rate of 15%, the final sample size was increased to 66, with 33 participants in each group. Sample size estimation was performed using PASS15.

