### Statistical analysis

2.9

All data from enrolled participants will be collected and analyzed. Descriptive statistics will be used to summarize baseline characteristics. The Shapiro–Wilk test will be applied to assess the normality of continuous variables. For normally distributed quantitative data, results will be presented as mean ± standard deviation (SD). For non-normally distributed data, results will be presented as median and interquartile range (IQR). Categorical variables will be expressed as frequencies and percentages, and between-group comparisons will be made using the chi-square test or Fisher’s exact test, as appropriate. To assess the treatment effects over time, linear mixed-effects models will be used to analyze repeated measures, accounting for both fixed effects (group, time, group × time interaction) and random effects. Both intention-to-treat (ITT) and per-protocol (PP) analyses will be conducted. For the ITT analysis, missing data will be handled using the Last Observation Carried Forward (LOCF) method, as previously used in acupuncture studies (40, 41). The PP analysis will include participants who complete the intervention and outcome assessments without major protocol deviations. Statistical significance will be defined as a two-sided *p*-value <0.05. All statistical analyses will be performed using SPSS version 24.0.

Lifestyle adherence scores will be summarized during the 16-week intervention period. The mean weekly adherence score will be calculated for each participant based on the Healthy Lifestyle Adherence Scoring System. Between-group differences in lifestyle adherence will be evaluated descriptively. Where appropriate, the mean lifestyle adherence score will be included as a covariate in adjusted analyses for clinical outcomes and rs-fMRI-related exploratory analyses. Sensitivity analyses may also be conducted to examine whether the main findings remain robust after accounting for lifestyle adherence or excluding participants with marked lifestyle non-compliance.

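### LOCF in the ITT analysis scores every woman without a week-16 AFC as zero change; if missing women resemble their arm, 15% loss shrinks the AFC difference by about 15%

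*Protocol article*

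**What the plan says.** All references are to the protocol article.

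- **Missing-data rule (2.9 Statistical analysis).** "For the ITT analysis, missing data will be handled using the Last Observation Carried Forward (LOCF) method". The reason given is earlier use in acupuncture studies. The rule makes no distinction by reason for missingness.
- **Model (2.9).** "To assess the treatment effects over time, linear mixed-effects models will be used to analyze repeated measures", with group, time and their interaction as fixed effects, plus random effects.
- **Visits (2.7.1 Primary outcome).** "At baseline (week 0), after the 16-week intervention (week 16) and at the end of the follow-up period (week 32), transvaginal ultrasound" is performed. No AFC is scheduled between weeks 0 and 16.
- **Quantity of interest (2.8 Sample size estimation).** "The sample size was calculated based on the primary outcome, namely the change in AFC from baseline to week 16".
- **Planning figures (2.8).** "Assuming a minimal clinically important difference of 1.8 between the two groups", and "Considering a potential dropout rate of 15%, the final sample size was increased to 66, with 33 participants in each group".
- **Per-protocol set (2.9).** "The PP analysis will include participants who complete the intervention and outcome assessments without major protocol deviations".

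**The concern.** With this visit schedule, the last AFC before week 16 is the baseline value. Carrying it forward makes the change to week 16 exactly zero by construction. The filled zeros count as full observations, so the analysis treats 33 women per arm as measured when fewer were.

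If those women would in fact have changed like the rest of their arm, the ITT estimate is pulled towards zero and the interval sits around the wrong value. If the arms lose different numbers, the size and direction of the bias depend on how much each arm changes.

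The filling is also unnecessary. A likelihood-based mixed model, planned in the same paragraph, uses incomplete records as they are and is valid under missing at random. What is at stake is mainly the reported effect and its interval. These matter because section 3 calls the findings preliminary, so a later trial may be planned from them.

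**Working it through.** **1. The plan's own sample size.** Section 2.8 gives 4.16 ± 0.86 and 3.00 ± 1.69, one-sided α 0.025 and power 90%. Only the second pair is described there as a change, so using both as change scores is an assumption.

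- Common SD = √((0.86² + 1.69²)/2) = 1.341. Difference = 4.16 − 3.00 = 1.16.
- n per arm = (0.86² + 1.69²)(1.960 + 1.282)²/1.16² = 28.08, which matches the stated 28 before rounding up.
- With 1.8 in place of 1.16, the same formula gives 11.66, so 12 per arm. A difference of 1.8 fits 28 per arm only with an SD of about 2.04 (t-based).
- 56/0.85 = 65.9, so 66, as stated.

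Two coherent planning pairs follow: difference 1.16 with SD 1.34, and difference 1.8 with SD 2.04. Both SDs are assumptions.

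**2. Expected difference under LOCF.** Let q be the fraction filled in an arm and m the mean change that the arm would have shown.

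LOCF difference = (1 − q_YYRM)·m_YYRM − (1 − q_control)·m_control

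With equal q, and missing women like their arm, this is (1 − q) times the true difference, whatever the control change. 15% of 33 is about 5 women, and 28/33 = 0.848.

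- 1.8 × 0.848 = 1.53
- 1.16 × 0.848 = 0.98
- At 5%, 10% and 20% missing, 1.8 becomes 1.71, 1.62 and 1.44.

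**3. Coverage and power.** Change scores were simulated with 33 per arm, 5 filled in each, a pooled t analysis and control change 0.

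| True difference, SD | Analysis | Mean estimate | 95% CI coverage | Power |
|---|---|---|---|---|
| 1.16, 1.34 | LOCF | 0.98 | 92% | 88% |
| 1.16, 1.34 | observed values | 1.16 | 95% | 89% |
| 1.8, 2.04 | LOCF | 1.53 | 92% | 90% |
| 1.8, 2.04 | observed values | 1.80 | 95% | 90% |

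In the first pair the average half-width is 0.62 under LOCF and 0.72 on observed values. A hand check agrees: the bias is 1.16 − 0.98 = 0.18, and the SD of the LOCF estimate is 1.341 × √56/33 = 0.304. Coverage is then Φ((0.62 + 0.18)/0.304) − Φ((−0.62 + 0.18)/0.304), about 0.92.

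A random-intercept mixed model with three visits (correlation 0.5 assumed, true effect 1.16, 400 runs) gave the same picture. LOCF estimated 0.97 with 93% coverage; observed values gave 1.14 with 96%.

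**4. If missing women gain nothing.** The treatment-policy difference is then itself 1.8 × 0.848 = 1.53. LOCF estimates it without shrinkage, while the unfilled analysis still gives 1.80. At SD 2.04 the unfilled bias is 0.27 with standard error 2.04 × √(2/28) = 0.545 and half-width about 1.09. Coverage is Φ((1.09 − 0.27)/0.545) − Φ((−1.09 − 0.27)/0.545), about 0.93.

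**5. Unequal loss (illustrations only; the documents give no such figures).**

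- Filled 20% against 10%, or the reverse, with a control change between −1 and +1: a true 1.8 is reported as 1.34 to 1.72.
- 8 YYRM and 2 control women filled, true difference 1.16, SD 1.34, control change 0: 1.16 × 25/33 = 0.88, with power 80% against 89% unfilled.
- No treatment effect, both arms losing 1.0 follicle, 8 against 2 filled: −25/33 + 31/33 = +0.18 in favour of YYRM. The one-sided false-positive rate is about 7.6% instead of 2.5%. With a loss of 0.5 follicle it is about 4.7%.

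**The case against.** The strongest reply is that women who leave a course of 16 weekly sessions receive less treatment and may gain little or nothing. Zero benefit is then close to the truth, LOCF gives about the right treatment-policy difference, and the mixed model on observed values overstates it (step 4). This stands. It is why the shrinkage can only be stated conditionally and why the remedy needs a no-benefit sensitivity analysis. It does not justify LOCF as the sole ITT rule, because LOCF imposes zero change on every missing woman in either arm, whatever the reason.

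Other points also stand in part:

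- Section 2.8 does not say that the 15% all occurs before week 16. Women lost later have an observed week-16 AFC, so 15% is the upper end of the planned loss.
- Power is almost unaffected under equal loss.
- The per-protocol analysis needs no filling, but it selects completers without major deviations and does not replace the ITT estimate.
- Women with only a baseline add almost nothing about change. The proposed analysis is therefore close to a completer analysis under missing at random.

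A reader might infer that coverage falls to 88%. That figure pairs 1.8 with SD 1.34, which does not give the plan's 28 per arm; with a coherent SD it is about 92%. A reader might also infer that conceptions under YYRM would be scored as treatment failures. The documents give no conception rate, and 2.7.1 sets no cycle window for the follow-up scans. How to treat values after conception is a separate choice of estimand.

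**Conclusion.** The point holds in a conditional form. It is certain from the text that LOCF gives zero change to every woman without a week-16 AFC. The loss of about 15% of the difference (1.8 to 1.53, or 1.16 to 0.98) and the fall in coverage to about 92% rest on three assumptions: all 15% are lost before week 16, the loss is equal in both arms, and missing women would have changed like their arm. The coverage figure also rests on the assumed SDs of 1.34 and 2.04.

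Two stronger readings are not supported. One is that the trial will report 1.53 whenever the truth is 1.8; this fails if women who leave gain less. The other is that LOCF is always conservative, or always harmful to YYRM; with unequal loss the direction depends on how each arm changes.

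This is a design choice worth changing. It does not threaten the trial's power under equal loss.

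**What to change.** In 2.9, replace the LOCF sentence with:

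> The primary ITT analysis fits the linear mixed-effects model to all observed values at weeks 0, 16 and 32 without filling missing values (missing at random). A sensitivity analysis assumes no benefit in women with missing week-16 AFC. LOCF is reported at most as a further sensitivity analysis.

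This needs no extra women, visits or data. Because recruitment is under way (2.3 Trial status), it should be made as a dated amendment before anyone sees outcome data by arm.

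There are two costs. The interval is wider: the half-width is about 0.72 instead of 0.62 at SD 1.34 with 5 of 33 women missing per arm. The primary estimate is also too large if women who leave gain less than completers; the no-benefit sensitivity analysis is there to show by how much.

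### LOCF is fixed as the ITT missing-data rule although the planned mixed model needs no imputation; it shrinks the week-16 AFC effect by roughly the dropout share and can distort it in either direction if dropout is unequal

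*Protocol article*

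**What the plan says.** Three places in the protocol article bear on the point.

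- **Section 2.9, Statistical analysis.** The treatment effect over time is to be estimated by a mixed model: "linear mixed-effects models will be used to analyze repeated measures, accounting for both fixed effects (group, time, group × time interaction) and random effects". Both ITT and per-protocol analyses are planned. For ITT, "missing data will be handled using the Last Observation Carried Forward (LOCF) method", and the only reason given is that earlier acupuncture studies used it.
- **Sections 2.7.1 and 2.7.2, outcomes.** AFC, the hormones and the scales are each assessed at weeks 0, 16 and 32, with no visit in between.
- **Section 2.8, Sample size estimation.** The primary endpoint is set here: "The sample size was calculated based on the primary outcome, namely the change in AFC from baseline to week 16". Attrition enters as a single figure, "Considering a potential dropout rate of 15" per cent, with no split by arm and no statement of when losses are expected.

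The sensitivity analyses named in section 2.9 are optional and concern lifestyle adherence.

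**The concern.** A likelihood-based mixed model already handles incomplete follow-up. A participant contributes whatever visits she has, and the estimates are valid if missingness depends only on observed data. Filling the gaps first removes that benefit and replaces it with a stronger and less plausible assumption.

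With this visit schedule the assumption is easy to state. A woman missing at week 16 has only her baseline to carry, so her primary outcome becomes exactly zero change. A woman seen at week 16 and lost afterwards is scored as keeping her week-16 value to week 32. A woman lost before week 16 carries baseline to both visits. The filled values then count as real measurements, so uncertainty is understated.

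At stake are the size of the week-16 effect, its comparability between arms if dropout differs, and the week-32 result.

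**Working it through.** **Inputs from the document.** Section 2.8 gives 4.16 (SD 0.86) for YYRM and 3.00 (SD 1.69) for waitlist, one-sided alpha 0.025, 90% power, 28 per group, 15% dropout and 33 per group.

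**Reproducing the plan's figure.** The difference between the quoted means is 4.16 − 3.00 = 1.16. The average variance is (0.86² + 1.69²)/2 = 1.798, so SD = 1.341. Then n = (0.86² + 1.69²)(1.960 + 1.282)²/1.16² = 28.08 per group. Taken as 28, this gives 89.9% power, and 56/0.85 = 65.9, rounded up to 66. The effect of 1.16 therefore reproduces the sample size. The stated difference of 1.8 does not, since it gives 12 per group. That mismatch is a separate matter; 1.16 is used below because it matches the planned N.

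**Week 16, formula.** Let D be the true effect, δ the change in the control arm, and d_T and d_C the shares missing week 16 in the YYRM and control arms, with dropout random within arm. Under LOCF each missing change is zero, so the expected estimate is

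(1 − d_T)(δ + D) − (1 − d_C)δ.

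**Equal dropout.** With d_T = d_C = 0.15 this reduces to 0.85 × D, whatever the drift:

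- D = 1.16: 0.85 × 1.16 = 0.99
- D = 1.8: 0.85 × 1.8 = 1.53

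A simulation (33 per arm, SD 1.34, baseline-adjusted week-16 analysis) gave 0.99 under LOCF and about 1.16 on observed data. Power was about 94% against 95% with an assumed baseline correlation of 0.5, and about 97% against 98% with 0.6.

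**Unequal dropout, no true effect.** With D = 0 the formula becomes δ(d_C − d_T). Both the drift and the imbalance are assumptions. For 25% missing in YYRM and 5% in control:

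| Assumed fall in AFC, both arms | LOCF false difference | Type I error, LOCF (nominal 5%) |
|---|---|---|
| 0 | 0 | about 5% |
| 0.25 | 0.25 × 0.20 = 0.05 | about 5% |
| 0.5 | 0.5 × 0.20 = 0.10 | about 6.5% |
| 1.0 | 1.0 × 0.20 = 0.20 | 11–12% |

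Reversing the dropout to 5% and 25% reverses the sign: −0.20 for a fall of 1.0. With a milder imbalance of 20% and 10%, type I error was 5.3%, 5.4% and 6.2% for falls of 0.25, 0.5 and 1.0. Observed-data analysis stayed at about 5% with a fall of 1.0 and either 25%/5% or 5%/25% dropout.

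**Week 32.** Let e be the share lost before week 16, l the share lost after it, and f the fraction of D still present at week 32. With equal losses in both arms, LOCF gives

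(1 − e − l)·f·D + l·D.

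For D = 1.16 and an effect that has fully faded (f = 0):

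- all 15% lost after week 16: 0.15 × 1.16 = 0.17
- all 15% lost before week 16: 0
- half and half: 0.075 × 1.16 = 0.09

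If the effect has half faded (true value 0.58), LOCF gives 0.85 × 0.58 + 0.15 × 1.16 = 0.67 when all losses come after week 16, and 0.85 × 0.58 = 0.49 when all come before.

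**The case against.** **The rule is conservative where the document's own figure applies.** With 15% dropout, equal between arms, LOCF attenuates the effect, does not inflate type I error and costs about one percentage point of power. This stands. The harm in that case is to the estimate, not to the test.

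**Doubled false positives.** A reader might infer that LOCF roughly doubles the false-positive rate in favour of moxibustion. The document does not support this. The 11–12% figure needs both a one-follicle fall in 16 weeks and 25% against 5% dropout. Section 2.8 gives neither, and its waitlist mean is only 3.00. The opposite imbalance biases against moxibustion. Unequal dropout is possible in an open-label trial where only one arm attends moxibustion sessions, but its direction cannot be predicted.

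**A manufactured week-32 result.** This too goes further than the figures allow. The document has one 15% dropout rate. If it is all spent before week 16 to obtain the 15% shrinkage, nothing is left to carry a week-16 effect forward.

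**Pregnancy.** A woman who conceives and has no valid early-follicular measurement would be scored as unchanged by LOCF. Treating her value as missing at random is also doubtful, so the mixed model alone does not solve this. It belongs in the sensitivity analysis.

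**Wording and scope.** The text does not literally say that LOCF-filled data enter the mixed model. It is the natural reading, since both rules share a paragraph and no other model for effects over time is given. The per-protocol analysis is a comparison without filled-in outcomes, but on a selected set. Missing-data sensitivity analyses are often left to an analysis plan, so their absence is not held against the article. The simulation used a single-visit baseline-adjusted analysis with dropout random within arm. It shows the LOCF bias but does not test the mixed model under outcome-related dropout.

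**Conclusion.** The point holds as a should-fix. Section 2.9 states an avoidable rule that biases the primary estimate, and its only support is precedent.

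- **Size tied to the document:** a 15% shrinkage of the week-16 effect (1.16 to 0.99), assuming all of the planned 15% dropout comes before week 16 and is equal between arms. The primary test is hardly affected.
- **Size under further assumptions:** a false difference equal to drift times the dropout imbalance, in either direction. It is 0.05 to 0.20 follicle over the range shown, and type I error is clearly raised only at the far end.
- **Week 32:** overstated persistence only for participants lost after week 16. With the effect fully faded, the overstatement lies between 0 and 0.17 follicle.

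It does not follow that LOCF systematically favours moxibustion or that it invalidates the primary test.

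**What to change.** Replace the LOCF sentence in section 2.9 with: *The ITT analysis fits the mixed model (REML) to all observed data of all randomised participants in their assigned arm, with no single imputation.*

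Add a multiple-imputation or delta-based sensitivity analysis for departures from missing at random, and say there how participants without a valid measurement because of pregnancy are treated. If LOCF is kept for comparability with earlier trials, label it a secondary sensitivity analysis.

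The cost is one replaced sentence and one added analysis. The model is already planned, and N stays at 66 because 56/0.85 already allows for the loss. Section 2.3 expects enrolment to run to December 2027, so the change can still be prespecified.

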### Intervention

2.6

Participants in both groups will receive lifestyle intervention during the 16-week intervention period. According to previous evidence from reproductive medicine (27–29), participants will be encouraged to adopt a balanced diet, engage in moderate physical activity suited to individual capacity, and maintain regular work and rest schedule. They will also be advised to avoid smoking, limit alcohol consumption. We designed a healthy lifestyle adherence scoring to assess adherence (see Supplementary S2 File). Lifestyle adherence will be assessed weekly throughout the 16-week intervention period using the Healthy Lifestyle Adherence Scoring System, which includes four domains: dietary modification, physical activity, sleep–wake regulation, and avoidance of harmful substances. Each domain will be scored from 0 to 2, with a total weekly score ranging from 0 to 8. Deviations from lifestyle recommendations will be documented during follow-up assessments.

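### Adjusting for, or excluding on, lifestyle adherence scored after randomisation can bias the estimated effect of allocation, so these analyses cannot show that the main result is robust

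*Protocol article*

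**What the plan says.** Under Intervention (2.6), both arms receive the lifestyle intervention. "Lifestyle adherence will be assessed weekly throughout the 16-week intervention period using the Healthy Lifestyle Adherence Scoring System", and "Each domain will be scored from 0 to 2, with a total weekly score ranging from 0 to 8".

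Under Statistical analysis (2.9), the treatment effect over time is assessed with linear mixed models, "accounting for both fixed effects (group, time, group × time interaction) and random effects", in ITT and per-protocol sets. Adherence is not among the listed terms. A later paragraph of 2.9 does three things with the participant's mean weekly score:

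- It compares the arms descriptively.
- It adds the score to adjusted models, on the condition that this is appropriate: "the mean lifestyle adherence score will be included as a covariate in adjusted analyses for clinical outcomes". This applies to clinical outcomes, which include the primary outcome AFC, and to the exploratory rs-fMRI analyses.
- It permits, but does not require, sensitivity analyses of whether the main findings hold after accounting for adherence or after "excluding participants with marked lifestyle non-compliance".

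Section 2.5 says that participants and clinicians cannot be blinded.

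**The concern.** A covariate in a between-arm model should not be something the treatment can change. The mean adherence score is built up during the same 16 weeks as the treatment, so allocation could affect it. One arm receives a weekly 40-minute hands-on treatment, nobody in the treatment room is blinded, and the Discussion concedes possible expectancy bias. One of the four scored domains is sleep–wake regulation, which could improve if the treatment helped mood or menopausal symptoms, both of which are secondary outcomes.

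Two things can then go wrong. If adherence itself affects AFC, adjustment removes the part of the treatment effect that runs through it. If an unmeasured trait such as motivation or general health drives both adherence and AFC, conditioning on adherence makes the arms differ on that trait although randomisation had balanced it. Excluding low adherers has the same problem in a cruder form.

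At stake is how the adjusted AFC result is read. The text presents these analyses as a test of robustness, and the condition for adjusting comes straight after a descriptive look at adherence by arm. An observed imbalance is the natural trigger for adjusting. If allocation caused that imbalance, this is also the situation in which adjusting can bias.

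**Working it through.** The protocol gives no figure for adherence or for its relation to any outcome, so there is no stated number to reproduce. The steps below show when bias arises and how large it could be under assumptions.

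**1. Scale.** Section 2.8 gives SDs of 0.86 and 1.69. Pooled SD = √[(0.86² + 1.69²)/2] = √1.798 = 1.341 follicles. As yardsticks, the previous-study means differ by 4.16 − 3.00 = 1.16, and the same section states a difference of 1.8. The planned 28 per group follows from 1.16 (power 89.9% at SD 1.341) and not from 1.8, which would need about 12 per group. That is a separate matter, so both yardsticks are shown.

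**2. Formula.** In a linear model, adding adherence changes the arm difference by

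change = (shift in adherence due to allocation) × (slope of outcome on adherence within arm).

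The slope includes both a direct effect of adherence and any association through a common cause. If either factor is zero, the change is zero.

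**3. Assumed range.** Both factors are assumptions.

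- Low: 0.25 SD × 0.2 SD per SD × 1.341 = 0.07 follicles, which is 6% of 1.16 or 4% of 1.8.
- High: 0.5 SD × 0.4 SD per SD × 1.341 = 0.27 follicles, which is 23% of 1.16 or 15% of 1.8.

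**4. Simulation of both procedures.** 400,000 participants were simulated per scenario. Assumptions: direct treatment effect 1.16; adherence SD 1.5 points within arm; direct slope, where present, 0.2 follicles per point; common cause, where present, worth 0.75 adherence points and 0.5 follicles per SD; exclusion of mean scores below 4.

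| Shift in adherence | Link to AFC | True total effect | Unadjusted | Adjusted | Low adherers excluded |
|---|---|---|---|---|---|
| 0 | both | 1.16 | 1.162 | 1.161 | 1.165 |
| 0.5 | none | 1.16 | 1.166 | 1.164 | 1.165 |
| 0.5 | common cause | 1.16 | 1.157 | 1.073 | 1.119 |
| 0.5 | direct | 1.26 | 1.259 | 1.160 | 1.219 |
| 0.5 | both | 1.26 | 1.253 | 1.071 | 1.179 |
| 1.0 | none | 1.16 | 1.157 | 1.157 | 1.157 |
| 1.0 | common cause | 1.16 | 1.162 | 0.996 | 1.099 |
| 1.0 | direct | 1.36 | 1.363 | 1.161 | 1.288 |
| 1.0 | both | 1.36 | 1.362 | 0.993 | 1.228 |

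The formula in step 2 agrees. For a one-point shift with both links, the slope is 0.2 + (0.75 × 0.5)/1.5² = 0.367, so the expected shortfall is 0.367. The simulation gives 1.36 − 0.993 = 0.367.

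The unadjusted estimate recovers the total effect in every row. Where allocation shifts adherence and a link exists, adjustment falls short by 0.09 to 0.37 follicles and exclusion by 0.04 to 0.13. In the other rows nothing is biased. All assumed links here are positive; a negative link would reverse the sign.

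**The case against.** The strongest case is that the plan does not do what a quick reading suggests. A reader might infer that the main ITT comparison is adjusted for adherence and so biased. The listed mixed model has no adherence term, so the documents do not support that. A reader might also take exclusion of non-compliers as a rule of the analysis; it is an optional sensitivity analysis set beside the ITT result. Nothing says that the adherence-adjusted estimate would replace the main one or be confirmatory. The Discussion calls the findings preliminary, and the rs-fMRI work is labelled exploratory. All of this stands.

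Nor do the documents say that moxibustion changes adherence. Both arms receive the lifestyle intervention, and controls have weekly sessions too. A shift of zero is consistent with the text, and the range in step 3 does not bound the bias. This also stands.

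A further objection is that the definitions of an appropriate case and of marked non-compliance may sit in a full protocol or SAP that is not shown. That is fair, and their absence is not the point here. The point is what the article does state: a covariate measured after randomisation is named for between-arm models of clinical outcomes, and adherence-based analyses are offered as a test of robustness. A threshold given elsewhere would make the rule less dependent on the data but would not cure the conditioning.

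Finally, accounting for a shared co-intervention is a recognisable supportive analysis. It is, provided that it is presented as answering a different question under its own assumptions. The text does not present it so.

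**Conclusion.** The concern holds for the adherence-adjusted and adherence-restricted analyses, and only for those. They can be biased for the effect of allocation if allocation shifts adherence and adherence is linked to the outcome. Agreement with the main result would not confirm it, and disagreement would not refute it.

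The size is unknown from the documents. The illustrative 0.07 to 0.27 follicles rests on an assumed adherence shift of 0.25 to 0.5 SD and an assumed slope of 0.2 to 0.4 SD per SD; zero is possible, and the direction depends on the unmeasured common causes. The sample size is unaffected. This is worth correcting because an adjusted result for the primary outcome is foreseen and its use is conditional on an unstated criterion.

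**What to change.** In section 2.9:

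- State that the between-arm comparisons of AFC and the other clinical outcomes are not conditioned on lifestyle adherence.
- Limit covariates in adjusted between-arm models to pre-randomisation variables, such as age and the baseline value of the outcome (where the model does not already use it as a response).
- Keep the descriptive summary of adherence by arm.
- Present any analysis that adjusts for adherence or excludes on it as exploratory only, for example as a mediation analysis with its assumptions stated, and remove the claim that it tests robustness.

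This rewords two sentences. Data collection and sample size do not change, and with enrolment expected to run to December 2027 it can be done before analysis. The cost is that the trial gives up a robustness check that some readers may expect.
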